## Abstract

**Background:**

Stereotactic ablative radiotherapy (SABR) has become an established treatment option for medically-inoperable early-stage (Stage I-IIA) non-small cell lung cancer (ES-NSCLC). SABR is able to obtain high rates of local control with low rates of symptomatic toxicity in this patient population. However, in a subset of patients with fibrotic interstitial lung disease (ILD), elevated rates of SABR-related toxicity and mortality have been described. The Assessment of Precision Irradiation in Early Non-Small Cell Lung Cancer and Interstitial Lung Disease (ASPIRE-ILD) study will conduct a thorough prospective evaluation of the clinical outcomes, toxicity, changes in diagnostic test parameters and patient-related outcomes following SABR for ES-NSCLC for patients with fibrotic ILD.

**Methods:**

ASPIRE-ILD is a single-arm Phase II prospective study. The accrual target is 39 adult patients with T1–2N0M0 non-small cell lung cancer with co-existing ILD who are not candidates for surgical excision. Pathological confirmation of diagnosis is strongly recommended but not strictly required. Enrolled patients will be stratified by ILD-related mortality risk. The starting SABR dose will be 50 Gy in 5 fractions every other day (biologically effective dose: 100 Gy_10_ or 217 Gy_3_), but the radiation dose can be de-escalated up to two times to 50 Gy in 10 fractions daily (75 Gy_10_ or 133 Gy_3_) and 45 Gy in 15 fractions daily (58 Gy_10_ or 90 Gy_3_). Dose de-escalation will occur if 2 or more of the first 7 patients in a cohort experiences grade 5 toxicity within 6 months of treatment. Similarly, dose de-escalation can also occur if 2 or more of the first 7 patients with a specific subtype of ILD experiences grade 5 toxicity within 6 months of treatment. The primary endpoint is overall survival. Secondary endpoints include toxicity (CTC-AE 4.0), progression-free survival, local control, patient-reported outcomes (cough severity and quality of life), rates of ILD exacerbation and changes in pulmonary function tests/high-resolution computed tomography findings post-SABR.

**Discussion:**

ASPIRE-ILD will be the first prospective study specifically designed to comprehensively evaluate the effectiveness and safety of SABR for ES-NSCLC in patients with co-existing ILD.

**Trial registration:**

Clinicaltrials.gov identifier: NCT03485378. Date of registration: April 2, 2018.

## Background

Non-small cell lung cancer (NSCLC) is the leading cause of cancer death in men and women worldwide. Approximately 20% of NSCLC patients present with early stage disease (T1 N0 or T2 N0), defined as tumors up to 5 cm in size, without nodal or distant metastases. For such patients, surgical resection has been considered the standard of care; however, many patients are ineligible for surgery because of co-morbid conditions.

Historically, alternatives to surgery have proven unsatisfactory. Most patients who were not candidates for surgery were treated with conventional radiotherapy, delivered as doses of 50–60 Gy in 4–6 weeks, with relatively rudimentary tumor targeting techniques. Conventional radiotherapy was associated with high rates of local recurrence, often 30–40% or higher, with only a minor improvement in long-term survival compared to observation alone [1, 2].

Stereotactic ablative radiotherapy (SABR) is a newer radiotherapy approach which uses modern radiotherapy planning and targeting technologies to precisely deliver larger, ablative doses of radiotherapy (up to 60 Gy in 3–8 fractions). SABR has been associated with high rates of local control, with many studies reporting 3-year local control of approximately 90% after SABR, comparable to results obtained with anatomic lobectomy [3]. Because of these promising outcomes, randomized trials are currently comparing SABR vs. surgery as first-line treatment for early-stage NSCLC (ES-NSCLC).

A major advantage of SABR is that in general, the toxicity profile is very favorable, even in patients with substantial co-morbid conditions. Radiation Therapy Oncology Group (RTOG) 0236, a North American phase II trial assessing outcomes with SABR for ES-NSCLC in patients who were unfit for surgery, demonstrated a risk of protocol-specified Grade 3 and 4 toxicities of 13 and 4% respectively, with no grade 5 toxicities [4]. Based on a large meta-analysis, the risk of treatment related death after SABR is estimated at < 1%. By comparison, after anatomic lobectomy, toxicity rates appear higher: with Grade 3 or 4 toxicity often approaching 50%, and 30-day mortality rates of 4–6% based on Medicare data, although this latter risk is lower at specialized high-volume centers [5, 6].

### Interstitial lung disease and SABR

Interstitial lung disease (ILD), also known as diffuse parenchymal lung disease, comprises a heterogeneous group of diseases characterized by a non-neoplastic, diffuse inflammatory and/or fibrotic pathology affecting the lung parenchyma, usually exhibiting a restrictive defect on pulmonary function testing with reduced gas exchange [7, 8].

ILD can be subdivided into fibrotic and non-fibrotic subtypes. Fibrotic subtypes include idiopathic pulmonary fibrosis (IPF), connective tissue disease-associated ILD (CTD-ILD), idiopathic non-specific interstitial pneumonia, hypersensitivity pneumonitis, and unclassifiable ILD. Fibrotic ILDs are characterized by reticulation, traction bronchiectasis, and frequently honeycombing on high-resolution computed tomography (HRCT). These fibrotic subtypes of ILD are the focus on this research protocol.

Patients with NSCLC and co-existing fibrotic ILD represent a high-risk group for any type of cancer treatment. Patients with ILD and NSCLC are at risk of both treatment-related toxicities and acute exacerbation of ILD [9], which can be life-threatening and even fatal. Despite the generally favorable toxicity profile of SABR, emerging data indicate that patients with pre-existing ILD are at particularly high risk of toxicity after SABR. A recent meta-analysis examined outcomes after several different treatments for early-stage lung cancer in patients with ILD [10]. Within the meta-analysis, 13 published studies (Additional file 1) assessed outcomes after SABR. Overall, the use of SABR in patients with early-stage NSCLC and pre-existing ILD was associated with a 25% risk of radiation pneumonitis (grade 3 or higher) and a 15% risk of treatment-related death. The risk may be highest in the subset of patients with IPF: SABR-related mortality was 33% in studies limited to IPF patients, and 14% in other studies that included only non-IPF fibrotic ILD, or a combination of IPF and non-IPF fibrotic ILD patients (*p* = 0.092).

However, the true rates of toxicity likely differ from the results of this meta-analysis, as nearly all the included studies were retrospective, a wide range of doses were used, and there was substantial variability in outcomes (e.g., treatment-related death ranged from 0 to 60% across studies). There is also risk of publication bias favoring the publication studies that show remarkable results (i.e. high rates of toxicity). Compounding these limitations, attribution of toxicity to radiation is difficult, since ILD exacerbations and radiation pneumonitis may result in similar clinical presentations.

Therefore, the true rates of toxicity of SABR in fibrotic ILD patients are likely higher than in the general population, but the precise extent of toxicity remains unknown.

### ILD severity

Even in the absence of lung cancer, the natural history of ILD is variable. Some patients survive many years with only a modest decline in lung function, whereas other patients experience rapid respiratory decline and death within a few short months.

The ILD-GAP (Gender-Age-Physiology) system (Table 1) is a prognostic model that takes into account disease type and severity, age, and gender, to predict survival in patients with the major subtypes of chronic ILD, including IPF [11]. The ILD-GAP index assigns an overall score between 0 and 8, with the majority of points assigned based on current pulmonary function. 3-year mortality ranges from 10% in patients with an index of 0–1 to 75% in patients with an index > 5. Notably, all patients with IPF or unclassifiable ILD have a minimum index of 2 in the ILD-GAP model, reflecting their inferior prognosis. We hypothesize that ILD subtype and severity of pulmonary impairment both influence the risk of radiation toxicity.

**Table 1 Tab1:** The ILD-GAP model, reproduced from Ryerson et al. [11]

Predictor		Points
ILD	ILD Subtype	
	• Idiopathic pulmonary fibrosis	0
	• Unclassifiable ILD	0
	• Connective tissue-ILD / idiopathic non-specific interstitial pneumonia	−2
	• Chronic hypersensitivity pneumonitis	−2
G	Gender	
	• Female	0
	• Male	1
A	Age	
	• ≤ 60	0
	• 61–65	1
	• > 65	2
P	Physiology	
	FVC, % predicted	
	• > 75%	0
	• 50–75%	1
	• < 50%	2
	DLCO, % predicted	
	• > 55%	0
	• 36–55%	1
	• ≤ 35%	2
	• Cannot perform	3
Total Possible Points		8

### Rationale for a study

For patients with ILD and concurrent early-stage lung cancer who are not candidates for surgery, these data showing high rates of toxicity have led to a difficult clinical dilemma, since there are few alternate treatment options. The option of delivering no treatment whatsoever, which avoids any risk of treatment-related toxicity, is associated with a high risk of death due to the lung cancer itself. The median survival for untreated stage I NSCLC is only 6–8 months, with 1-year mortality of 60–70% [12], much higher than the risks associated with SABR treatment. For example, in one study of untreated patients with NSCLC in the U.S. National Cancer Database, the median survival for patients with stage I NSCLC who were unfit for an operation was 7.6 months [13]. This suggests that even in patients with an ILD-GAP score > 5, the risk of death due to lung cancer within 1 year exceeds the risk of death due to ILD or complications of SABR.

As a result, patients with ILD and early-stage NSCLC are often advised, after discussion of their case at a multidisciplinary conference, that treatment with SABR provides the best chance of local control and cure, but that SABR is associated with an appreciable risk of treatment-related toxicity. For patients undergoing SABR under this scenario, the optimal dose and fractionation is unknown.

It is possible that currently-used doses and fractionations of SABR, when given with strict planning criteria to minimize the risk of lung toxicity, have only a modest risk of treatment-related toxicity and represent the best possible approach.

Alternatively, it may be necessary to reduce the dose of SABR, at the risk of compromising tumor control. Adjustments to the SABR fractionation schedule may reduce the risk of toxicity, while still maintaining some benefit. Radiation dose is expressed in Gray (Gy), with most SABR treatments delivering approximately a total dose 50–60 Gy. This total dose is divided up into smaller individual fractions of radiation. Conventional radiotherapy employs fraction sizes of approximately 2 Gy per day, 5 days per week, and would require 30 fractions to deliver 60 Gy. This prolonged treatment time (i.e. 6 weeks of treatment) may allow for tumor repopulation, compromising treatment outcomes. With SABR, common fractionations include 54 Gy in 3 fractions (i.e. 18 Gy per fraction), 48 Gy in 4 fractions (i.e. 12 Gy per fraction) and 60 Gy in 8 fractions (i.e. 7.5 Gy per day). SABR fractions are often given every second day (or even more widely spaced) to maximize the time for normal tissue repair between fractions.

To compare the potency of these different radiation dose fractionations, a formula called the biologically effective dose (BED) is used. BED takes into account the total number of fractions, the dose per fraction, and the intrinsic radiation response curve of the individual tissues treated. BED is calculated according to the formula $$ {BED}_{\alpha /\beta }= nd\left(1+\frac{d}{\alpha /\beta}\right) $$, where *α*/*β* is the alpha/beta ratio of the tissue (assumed to be 10 Gy for NSCLC and 3 Gy for normal lung tissue), *n* is the total number of fractions of radiation therapy and *d* is the dose per fraction.

The BED_10_ is used to predict the response of tumor, and also of acutely-responding normal tissues (e.g. skin and mucosa). A higher BED_10_ is associated with a higher chance of local control, and a value of BED_10_ ≥ 100 is considered a minimum threshold for SABR [14]. The BED_3_ is used to predict the response of normal lung parenchyma (i.e. the risk of radiation pneumonitis). A lower BED_3_ is expected to be associated with a reduced risk of pneumonitis. However, efforts to reduce the BED_3_ will also lead to reductions in BED_10_, compromising the effectiveness of SABR. (For specific BED_10_ and BED_3_ values used in the studies included in the meta-analysis, see Additional file 1).

### Rationale for starting at a standard SABR dose

During the design of this trial in 2016–17, several options were considered and ultimately discussed at a meeting of the Canadian Pulmonary Radiotherapy Investigators’ (CAPRI) Group at the September 2017 Canadian Association of Radiation Oncology Annual Meeting. Two main alternative approaches were considered:
**Option 1**: Conduct a phase II trial using a standard dose of SABR that has a high chance of local control; specifically, 50 Gy in 5 fractions (BED_10_ = 100), with careful attention to minimization of lung dose, and built-in dose de-escalation if toxicity is excessive.**Option 2.** Conduct a phase I trial starting with a less-potent dose of radiation to potentially minimize toxicity, and then escalate the dose thereafter. This would be expected to result in lower local control.

The CAPRI concluded that option 2 was unfavorable for 3 reasons: it would subject patients to a higher risk of local recurrence, which itself could be expected to be fatal; it is unclear that reducing to the lower dose levels would impact toxicity substantially; and many attendees stated that a common current approach outside of a trial is to offer full-dose radiotherapy after a careful discussion with patients.

There is precedent for this approach, as two other phase I trials of SABR have started at therapeutic doses: RTOG 0813 for central tumors (started at 50 Gy in 5 fractions before escalating to 60 Gy in 5 fractions) and SUNSET for ultra-central tumors (starting at 60 Gy in 8 fractions, currently underway) [15].

### Rationale for primary endpoint and study design

Important outcomes for patients with NSCLC and ILD include both toxicity and oncologic outcomes, and both were considered as possible primary endpoints.

Pulmonary toxicity was not chosen as a primary endpoint because it is very difficult to distinguish between radiation pneumonitis and ILD exacerbations. The patients included herein are expected to develop ILD exacerbations as part of the natural history of their ILD, and they are at risk of ILD-related death, which is difficult to distinguish from pneumonitis-related death. Erroneous attribution of ILD exacerbations to radiation could lead to the incorrect conclusion that the radiation dose should be lowered. In essence, the subjectivity of assigning the cause of toxicity should not be part of the primary outcome due to the risk of misattribution. However, pulmonary toxicity outcomes will be closely monitored in this trial.

Overall survival (OS) was chosen as the primary outcome as it objectively reflects the potential benefits of treatment (i.e. extended survival), the harms of treatment (grade 5 toxicity), and the natural history of the ILD disease process itself. Since the median survival of untreated Stage I NSCLC in inoperable patients is consistently reported as < 1 year (as noted above), we hypothesize that the use of SABR can achieve a median OS of > 1 year in patients with ILD. Though pulmonary toxicity is not to be the primary outcome in this trial, it will nevertheless be closely monitored to determine whether subsequently-enrolled patients will receive a deescalated radiation regimen.

SABR will be considered worthwhile if median OS is > 1 year with an acceptable risk of toxicity, defined as a grade 3 or 4 pulmonary toxicity rate of less than 35% and a risk of treatment-related death of less than 15%.

## Methods/design

This is a prospective phase II study of SABR in patients with co-existent interstitial lung disease, to determine oncologic and toxicity outcomes. Patients will be divided into 3 separate cohorts based on the ILD-GAP index (Table 1).

The Study Schema can be found in Fig. 1. The required sample size is 39. Patients who meet eligibility criteria but decline to pursue radiation and patients for whom SABR cannot be delivered at the recommended doses due to inacceptable doses to normal tissues at risk will be asked to consent to limited ongoing follow-up only.

**Fig. 1 Fig1:**
[figure not shown]
Study Schema. Patients with T1–2N0M0 non-small cell lung cancer and co-existing fibrotic interstitial lung disease will be enrolled in this single-arm study. Analysis will be stratified by interstitial lung disease severity. NSCLC: non-small cell lung cancer, ILD: interstitial lung disease, ILD-GAP: interstitial lung disease – gender/age/physiology model

## Objectives

### Primary endpoint

Overall survival: defined as time from enrollment to death from any cause

### Secondary endpoints

CTC-AE 4.0 toxicity
Including risk of treatment-related mortality within 6 months of radiotherapy.Including an analysis of pulmonary toxicity stratified by anti-fibrotic drug useProgression-free survival: defined as time from enrollment to death from any cause or any progression of disease (local, regional or distant)Local controlChanges in cough severity (using a 10 cm visual analogue scale)Rates of acute-exacerbation of IPF (in IPF patients), defined using Collard 2016 criteria:
Acute worsening or development of dyspnea > 1 month durationComputed tomography (CT) with new bilateral ground-glass opacity and/or consolidation superimposed on a background pattern consistent with usual interstitial pneumonia patternDeterioration not fully explained by cardiac failure or fluid overloadRates of acute-exacerbation of ILD (in non-IPF patients), defined using the same Collard 2016 criteriaQuality of Life (Functional Assessment of Cancer Therapy – Lung (FACT-L) and EuroQol 5-Dimensional 5-Level (EQ-5D-5L))Changes in ILD severity as qualitatively measured on HRCT (i.e. HRCT fibrosis score and HRCT total disease score)Changes in pulmonary function tests, including diffusing capacity of the lungs for carbon monoxide (DLCO), forced expiratory volume in 1 s (FEV_1_), and forced vital capacity (FVC).Exploratory quantitative analysis of HRCT features (i.e. radiomics)Analysis of outcomes for patients who otherwise meet the study enrollment criteria but decline radiotherapy.

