## Patient selection

### Inclusion criteria

Stage T1–2, N0, M0 (American Joint Committee on Cancer (AJCC) Staging, 8th Edition – i.e. tumor size ≤5 cm) prior to registration.Not a candidate for surgical resection, determined by any of the following:
Consultation with a thoracic surgeonDiscussion at multidisciplinary tumour conference with a surgeon presentPatient refusal of surgeryPathologically (histologically or cytologically) proven diagnosis of non-small cell lung cancer (NSCLC) is not required, but strongly recommended.
If the risk of biopsy is unacceptable, pathologic confirmation is not required providing there is growth over time on CT imaging and/or fluorodeoxyglucose (FDG) avidity that is strongly suggestive of a primary NSCLC.Eastern Cooperative Oncology Group (ECOG) performance status 0–3.Age ≥ 18.Life expectancy > 6 months.Fibrotic interstitial lung disease of any subtype, as diagnosed by a respirologist/pulmonologist and confirmed by central review.

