### Central review

A central review of the standardized clinical data, HRCT, and any previous lung biopsies (if available) will be done to confirm subtype of ILD. The central review team will include a pathologist, respirologist, and radiologist.

The following information will be required for central review:
Clinical/Laboratory Data: Including clinical history, symptoms with date of onset, smoking history (including pack years and quit date), exposures, CTD features, serology (normal and abnormal), pulmonary function tests, and the subtype of ILD as determined by the treating respirologist.Pathology: slides (to be returned) and pathology reportsRadiology: Digital Imaging and Communications in Medicine (DICOM) images of thoracic CT scans (through Quantitative Imaging for Personalized Cancer Medicine (QIPCM)) and radiology reports

Patients will be assigned to a category of fibrotic ILD (i.e. IPF, idiopathic non-specific interstitial pneumonia, CTD-ILD, hypersensitivity pneumonitis, Unclassifiable ILD/other) and an ILD-GAP score will be assigned.

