### Causality of pre-specified toxicity endpoints

Any Grade 3–5 toxicity listed in Table 4 will **automatically** be considered to be possibly, probably or definitely related to treatment, unless there is clear evidence that the adverse event is unrelated or unlikely to be related. The latter instance may occur, for example, in the case of a cardiac event in a patient with an upper lobe tumor and negligible heart dose, or esophageal issues in a patient who received negligible esophageal dose. The final decision will be made by the members of the data safety monitoring committee (DSMC). See below for causality definitions.

**Table 4 Tab4:** Pre-specified adverse events

Structure	Adverse Event
Cardiac and Pericardial	• Acute coronary syndrome
	• Aortic valve disease
	• Atrial fibrillation
	• Atrial flutter
	• Atrioventricular block
	• Conduction disorder
	• Constrictive pericarditis
	• Heart failure
	• Left ventricular systolic dysfunction
	• Myocarditis
	• Pericardial effusion
	• Pericardial tamponade
	• Pericarditis
	• Cardiomyopathy
	• Cardiac disorders-others
Gastrointestinal	• Dyspepsia
	• Dysphagia
	• Esophageal fistula
	• Esophageal hemorrhage
	• Esophageal necrosis
	• Esophageal obstruction
	• Esophageal stenosis
	• Esophageal perforation
	• Esophagitis
Pulmonary/mediastinal	• Atelectasis
	• Bronchial fistula
	• Bronchial obstruction
	• Bronchopleural fistula
	• Bronchopulmonary hemorrhage
	• Dyspnea
	• ILD or IPF exacerbation
	• Pneumonitis
	• Tracheal/Pulmonary fistula
	• Tracheal stenosis
	• Mediastinal hemorrhage
	• Pulmonary disorders-others

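### The non-IPF acute-exacerbation endpoint requires a usual interstitial pneumonia background that eligible patients need not have, and its dyspnea criterion of more than one month conflicts with the word acute

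*Protocol article*

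**What the plan says.** The Secondary endpoints section defines acute exacerbation of IPF by three criteria taken from a cited 2016 definition:

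- a respiratory criterion, acute "worsening or development of dyspnea > 1 month" in duration;
- a CT criterion, new bilateral ground-glass change and/or consolidation "superimposed on a background pattern consistent with usual interstitial pneumonia" pattern;
- deterioration not fully accounted for by heart failure or fluid overload.

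The same list then names rates "of acute-exacerbation of ILD (in non-IPF patients), defined using the same" criteria. No adaptation for non-IPF disease is given.

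The Inclusion criteria admit "Fibrotic interstitial lung disease of any subtype". Central review places each patient in one of these categories: "IPF, idiopathic non-specific interstitial pneumonia, CTD-ILD, hypersensitivity pneumonitis, Unclassifiable ILD/other". The Background says that patients with ILD and NSCLC are at risk of "acute exacerbation of ILD [9], which can be life-threatening and even fatal". Table 4, under the causality of pre-specified toxicity endpoints, separately lists "ILD or IPF exacerbation" as an adverse event and attaches no imaging or duration condition.

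**The concern.** An endpoint definition has to be attainable by every patient whose rate it is meant to measure. Here a criterion written for IPF is carried over to patients who, by construction, do not have IPF. Some of them fall in categories for which the protocol never requires or describes a UIP background. For a patient without that background the endpoint is zero by definition, whatever happens clinically.

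The duration wording is a second, independent problem. An acute event that must last more than a month is a contradiction in terms. The literal rule removes the events with the shortest course, including any that are quickly fatal.

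At stake is a named safety endpoint reported separately for IPF and non-IPF patients. The ILD severity section hypothesizes that subtype influences the risk of radiation toxicity, so readers will set the two rates side by side. The protocol also stresses how hard exacerbation is to separate from radiation pneumonitis, which makes a workable definition more important here than usual.

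**Working it through.** The protocol states no exacerbation rate, null value or power for this endpoint, so there is no figure to reproduce. The check is mainly textual.

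**Step 1: CT criterion against the population.** The criterion needs a UIP-consistent background (Secondary endpoints). Eligibility needs only fibrotic ILD (Inclusion criteria). Central review expects categories other than IPF, one of them named for a different pattern, non-specific interstitial pneumonia. Nothing in the article says that all non-IPF patients will show a UIP-consistent pattern. Eligible patients can therefore exist who can never satisfy the CT criterion. Because an added requirement can remove events but not create them, the direction of the bias is fixed: downward.

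**Step 2: duration criterion against the clinical description.** The natural reading of the respiratory criterion is that the episode of dyspnea must last more than one month. A patient who dies or recovers within a month of onset fails it. The Background says exacerbations can be fatal but gives no time from onset to death. The criterion sits in the IPF definition and is inherited by the non-IPF one, so both rates are affected.

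**Step 3: can the size be stated?** Let u be the share of non-IPF exacerbations occurring on a UIP-consistent background, and s the share of those with dyspnea lasting more than one month. Then

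- share counted = u × s
- share missed = 1 − u × s

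The documents give neither u nor s. With purely assumed values:

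| u | s | counted | missed |
|---|---|---|---|
| 0.2 | 0.5 | 0.2 × 0.5 = 10% | 90% |
| 0.5 | 0.9 | 0.5 × 0.9 = 45% | 55% |
| 0.8 | 0.9 | 0.8 × 0.9 = 72% | 28% |

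More than half are missed only if u × s is below 0.50. The assumed range falls on both sides of that line, so the protocol fixes the direction but not the size.

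**Step 4: where else the events are recorded.**

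- Table 4 lists exacerbation, dyspnea, pneumonitis and other pulmonary disorders without these conditions. At grade 3–5 they are presumed treatment-related unless there is clear evidence otherwise.
- Treatment-related mortality within 6 months is its own secondary item.
- Overall survival counts every death.
- The sample size, the criteria for calling SABR worthwhile and the de-escalation rule are not expressed in terms of this exacerbation definition.

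**The case against.** The strongest reply has four parts.

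*The share without a UIP background is unknown and may be small.* The Background describes fibrotic ILD as a group by reticulation, traction bronchiectasis and often honeycombing. It does not confine UIP to IPF, and the criterion asks only for consistency with UIP. This stands against any claim about size. A reader might infer that most non-IPF exacerbations are lost; Step 3 shows that the documents do not support that. It does not answer the defect itself, because the definition still excludes any eligible patient who lacks the pattern.

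*The duration may attach only to newly developed dyspnea.* On that parse, acute worsening of existing dyspnea carries no time limit. The sentence allows this, so the exclusion is not certain for every patient. But new dyspnea would still have to last over a month, and a criterion open to two readings will be applied inconsistently. Whether the wording departs from the cited definition cannot be checked here, and the point does not rely on it.

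*Serious events are captured elsewhere.* This is correct and limits the consequence. A reader might infer that all rapidly fatal exacerbations vanish from the trial. They do not: at most they drop out of this one rate, and only if fatal within a month of onset. Other capture does not repair the named endpoint, however. Table 4 gives no definition of exacerbation, so the two counts may disagree.

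*No comparison is planned.* A reader might infer that the trial would produce a false IPF versus non-IPF test result. The article plans two separate rates and no test between them, and the toxicity hypothesis can be examined through CTCAE data. What remains is that two rates shown together would differ partly through definition.

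An article may leave detail to the full protocol, but that does not help here: the article states an explicit rule, and the rule does not fit the patients it is applied to.

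**Conclusion.** The concern holds as a defect in a secondary endpoint definition. Read as written, eligible non-IPF patients without a UIP-consistent background cannot have an event, so the non-IPF rate can only be biased downward. The size of that bias cannot be computed from the documents. The duration criterion conflicts with the word acute and, on its natural reading, excludes exacerbations that end within a month of onset in both groups.

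The conclusion rests on two readings: that the same criteria means all three criteria unchanged, and that the one-month duration applies to the episode of dyspnea. The first is what the text says; the second is the natural but not the only parse. The primary endpoint, sample size and adverse-event recording are unaffected. It should be corrected, but it does not threaten the trial's main conclusion.

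**What to change.** 1. For non-IPF patients, replace the CT background requirement with new bilateral ground-glass change and/or consolidation over and above the fibrotic ILD pattern on that patient's own baseline HRCT.
2. Reconcile the dyspnea criterion with the word acute and with the cited definition, for IPF and non-IPF patients together, so that an exacerbation ending in death or recovery within a month of onset is counted.
3. Leave the Table 4 adverse-event list unchanged. Carrying a CT-based definition into it could narrow the presumption of relatedness for grade 3–5 events, which feeds the count of grade 5 treatment-related toxicity behind the de-escalation rule.

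The cost is endpoint wording only. Baseline HRCT and centrally reviewed subtype are already collected, and no change to sample size or primary analysis follows. The new wording should be settled before exacerbations are classified for analysis, so that all patients are judged by one rule.
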